### Secondary outcomes

The relationship between pacing site, reduction of AF episodes, quality of life, heart failure, cerebrovascular accident (CVA), number of cardioversions, frequency and duration of hospital admission and AF progression to persistent AF will be examined.

### Randomization

Enrolled patients will be added to a tailor-made website, which will automatically randomize participants to either the control group (RAA pacing) or experimental group (dCS pacing). Randomization is stratified for all participating medical centers.

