## Background

Sinus node disease is defined as an intrinsic, symptomatic form of sinus node dysfunction and was first described by Wenckebach in 1923. It is also known as the sick sinus syndrome (SSS) and develops at a mean age of 68 years [1–5].

It is expected that the incidence of SSS will continue to increase due to ageing of the population, as impulse formation within the sinus node declines over time [6]. This may be caused by destruction of the sinus node itself or ischemia, inflammation or degeneration of the surrounding nerves or ganglia. If more than 90% of the sinus node tissue is damaged, SSS develops. However, sinus node dysfunction may also have extrinsic causes including antiarrhythmic drug usage, electrolyte disturbances, hypothermia, hypothyroidism, increased intracranial pressure and excessive vagal tone [6]. Sinus node disease accounts at present for approximately 35 to 45% of the pacemaker implantations in Europe and the United States and it is expected that the number of subjects requiring cardiac pacing will continue to rise in the coming decades [1, 6–9]. Within this group, 30% have symptomatic paroxysmal atrial fibrillation (PAF) [10]. The combination of sinus bradycardia or sinoatrial block and paroxysms of atrial fibrillation (AF) is also known as the brady-tachy syndrome [1, 4]. AF is associated with severe implications including heart failure and stroke; 20% of all strokes can be attributed to AF and patients with AF have a five-fold higher risk of stroke [11].

A meta-analysis by Coplen *et al*. revealed that only 50% of the PAF patients who were treated with anti-arrhythmic drugs remained in sinus rhythm (SR) during a one-year follow-up period [12]. In addition, the heart rate of SSS patients, who already have a sinus bradycardia, will become even lower when using antiarrhythmic drugs for symptomatic episodes of AF. In the PAF study, atrioventricular junctional (AVJ) ablation with DDD pacemaker implantation was compared with pharmacological treatment [13]. Quality of life scores were higher in the non-pharmacological group and these patients were also less symptomatic.

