### Study population

Patients of 18 years or older, with either intrinsic or extrinsic (antiarrhythmic drug-induced) SSS and at least one PAF episode of 30 seconds or more within six months before enrollment, will be eligible to participate in the study. PAF episodes will be assessed by 24-hour Holter recording, preceding enrollment.

All patients with a clinically estimated life expectancy of five years or less or mental and/or physical inability to accomplish the follow-up period, will be excluded from participation in the Riverleft study. Left ventricular ejection fraction of 40% or less, malignancies and congenital heart defects are also exclusion criteria. Furthermore, chronic obstructive pulmonary disease classified as GOLD 4 and renal disease resulting in a glomerular filtration rate of ≤30 mL/min or creatinine value of ≥250 umol/L will prevent candidates from participation. The local investigator will only enroll eligible subjects after a signed informed consent form (ICF) is obtained.

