### Primary outcomes

The main objective of this study is to determine the effect of dCS pacing compared to RAA pacing for the prevention of recurrent AF episodes. Total number of AF recurrences and time between recurrences will be assessed and compared between both groups.

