### Study phases

#### Pre-randomization

Patients who meet the inclusion criteria will be approached by the local investigator or nurse practitioner to explain the Riverleft study and to hand over a patient information form. Candidates will be asked to participate in this study after a one-week reflection period. The nurse practitioner will call back or visit the candidate if the patient is hospitalized, and will obtain a signed ICF. Due to the obligation to give the patient a reflection period of seven days, pacemaker implantations in an acute setting cannot be enrolled in this study.

Eligible candidates, who agreed to participate in the study, will be scheduled for a visit to a cardiologist. During the intake visit, the patient will be asked to complete a health survey questionnaire (SF-36). Further examination includes an electrocardiogram (ECG) and cardiac echocardiography. Left atrial size will be determined in long-axis parasternal view and apical two-chamber view. In addition, left ventricular end systolic and left ventricular end diastolic diameter will be measured and diastolic function will be assessed by computing the ratio of early to late diastolic filling, the E/A ratio.

Medical records will be reviewed to determine the moment of SSS and PAF onset, to document accompanying symptoms during an AF episode and to assess risk factors, prescribed antiarrhythmic drugs and major events which are defined as CVA’s, transient ischemic attacks (TIA) or myocardial infarction. Practical and technological aspects of the selected pacemaker and HM will be explained by the pacemaker technician.

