### Statistical analysis

This study is designed to compare recurrences of AF episodes between two treatment groups. Therefore the Fisher’s exact test will be used for this categorical data to assess the difference in AF recurrence. Continuous data regarding duration and total number of AF recurrences will be analyzed by the Student’s t-test. Kaplan-Meier curves will be constructed to compare event-free survival between both groups. Secondary outcomes will be analyzed by a multivariate analysis. A *P* value of 0.05 is considered to be statistically significant.

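### The stated tests for the number and duration of AF recurrences use no baseline AF measure, so they give up precision that a screening Holter could supply

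*Protocol article*

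**What the plan says.** All references are to the protocol article.

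- **Study population:** patients may have "either intrinsic or extrinsic (antiarrhythmic drug-induced) SSS and at least one PAF episode of 30 seconds or more". No upper limit on the number or duration of episodes is given. On measurement, "PAF episodes will be assessed by 24-hour Holter recording, preceding enrollment".
- **Pre-randomization:** "Medical records will be reviewed to determine the moment of SSS and PAF onset". Symptoms, risk factors, antiarrhythmic drugs and major events are also collected. An AF episode count or duration is not on the list.
- **Randomization:** "Randomization is stratified for all participating medical centers". This is the only stratification factor named.
- **Primary outcomes:** "Total number of AF recurrences and time between recurrences will be assessed and compared between both groups".
- **Statistical analysis:** AF recurrence is compared by Fisher's exact test. "Continuous data regarding duration and total number of AF recurrences will be analyzed" by Student's t-test. Kaplan-Meier curves are added, and a multivariate analysis, with covariates not named, is assigned to the secondary outcomes.

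**The concern.** The primary outcome is a per-patient AF count over 33 months (36 months less the three-month run-in). Entry rules with only a floor admit patients whose AF frequency differs widely, and a patient's earlier AF frequency is a natural predictor of the later count. A recording made to assess AF is planned for every patient before enrolment, yet the tests named for the primary outcome cannot use it. They do not use centre either, although centre is the stratification factor.

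What is at stake is precision. Variation between patients that a baseline measure could explain stays in the error term. The arm difference is then estimated less exactly than the same patients would allow, and a chance imbalance in baseline AF is not corrected.

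**Working it through.** **1. The plan's own figures.** The Sample size section gives 300 patients for 80% power and 330 enrolled for 10% dropout. It states no effect size, event rate or SD, so 300 cannot be reproduced, only inverted. With 150 per arm and two-sided 0.05 (1:1 allocation and two-sidedness are assumed), the detectable standardised difference is (1.960 + 0.842) × √(2/150) = 0.323 SD. For dropout, 300 × 1.10 = 330, while 300/0.90 rounds up to 334; the gap is small and does not affect this point.

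**2. Gain from adjustment.** In a linear model with one baseline covariate, the variance of the arm difference is multiplied by 1 − r², where r is the correlation of baseline with follow-up, here both on the log scale. Power at 300 patients is Φ(2.802/√(1 − r²) − 1.960). The number giving the precision of 300 adjusted patients without adjustment is 300/(1 − r²).

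| r (assumed) | Variance cut | Power at 300 | Unadjusted N of equal precision |
|---|---|---|---|
| 0.1 | 1% | 80.4% | 303 |
| 0.2 | 4% | 81.6% | 312 |
| 0.3 | 9% | 83.6% | 330 |
| 0.5 | 25% | 89.9% | 400 |
| 0.7 | 49% | 97.5% | 588 |

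**3. Could a 24-hour count reach such correlations?** An illustrative simulation used 150 per arm, a log-normal patient rate, Poisson counts, a rate ratio of 0.65 and 2,000 runs per row. All of these are assumptions.

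| SD of log rate | Mean count, 33 months | r (log scale) | Power: t-test, raw count | Power: t-test, log count | Power: log count, adjusted |
|---|---|---|---|---|---|
| 1.0 | 100 | 0.28 | 82.5% | 95.7% | 97.0% |
| 1.0 | 1,000 | 0.63 | 82.2% | 95.4% | 99.7% |
| 1.5 | 100 | 0.37 | 33.1% | 67.1% | 73.8% |
| 1.5 | 1,000 | 0.69 | 34.1% | 70.1% | 92.2% |

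The simulation holds each patient's underlying rate constant from screening through follow-up, apart from the treatment effect. That favours the Holter as a predictor. Much of the improvement over the raw-count t-test comes from the change of scale; the last two columns isolate what adjustment adds, from about 1 to 22 percentage points.

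**4. Is centre-only stratification a fault?** With 165 per arm, the SD of a standardised baseline difference is √(2/165) = 0.110. The chance of a difference beyond 0.2 SD in either direction is about 7%. Adding a stratum while keeping the same unadjusted tests would not deliver the gain in step 2, which comes from using the covariate in the analysis.

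**The case against.** **Scope.** This is a condensed article, and covariates are often left to the analysis plan. That would dispose of the point if the article were silent. It is not: it names two tests that take no covariate for the primary outcome and places multivariate analysis with the secondary ones. A fuller plan may differ, in which case the two should be reconciled.

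**Size.** r is wholly assumed. One 24-hour recording, made before pacing and before the drug regimen is settled, may predict 33 months of device-detected AF only weakly. At r = 0.2 the gain is under two points of power. This stands. It also stands that the r² rule applies only if the outcome itself is put on a log scale, with a count model as an approximate parallel. It does not carry over to the raw-count t-test, Fisher's exact test or the Kaplan-Meier curves.

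**Stronger readings.** A reader might infer more than the text supports:

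- That near-continuous AF is admitted. The missing upper limit does not say this. Entry is for paroxysmal AF, and progression to persistent AF is a secondary outcome.
- That a baseline AF burden is already in hand and ignored. The Holter is described only as assessing PAF episodes; a recorded count or duration is not mentioned.
- That the randomisation is deficient. Step 4 shows that it is not, and randomisation keeps the comparison unbiased.
- That enrolling drug-induced SSS contradicts the Background, where "Sinus node disease is defined as an intrinsic, symptomatic form of sinus node dysfunction". The same section goes on to list antiarrhythmic drugs among extrinsic causes of sinus node dysfunction, and Study population openly admits both types. This is a stated choice of population. Nothing in the article shows that SSS type predicts AF recurrence, so a separate effect by type would be a preference.

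**Conclusion.** The point holds as one of efficiency. The stated primary comparison of AF number and duration leaves out a baseline AF measure that the planned Holter could supply, and also leaves out centre. For r of 0.2, 0.3 and 0.5, adjustment would lift 80% power to about 82%, 84% and 90%; at r = 0.5, 300 patients would give the precision of 400 unadjusted. The result rests on an assumed r, on a log-scale outcome and on two-sided 0.05 with equal arms. The documents cannot settle where in this range the trial lies. No bias or invalidity follows. The change is worth making because it is nearly free; the trial does not fail without it.

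**What to change.** 1. Enter the number and total duration of AF episodes on the screening Holter on the trial website before randomisation.
2. In Statistical analysis, replace the unadjusted t-test with a prespecified model on a suitable scale: negative binomial regression for the count, and log(1 + y) regression for duration (or for both). Adjust for log(1 + Holter AF measure) and for centre.
3. SSS type may be added as a covariate, with no separate subgroup claim attached.

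The cost is two website fields and slightly more analysis work, with no extra patients, visits or procedures. Trial status says that inclusion had not begun, so on the article's account the fields could be in place from the first patient. The downside is that the gain may be small if a single 24-hour Holter predicts later AF poorly.

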**Methods/Design:**

This study is designed as a multicenter, randomized controlled trial. Patients with sick sinus syndrome and at least one atrial fibrillation episode of 30 seconds or more in the six months before recruitment will be eligible for participation in this study.

All participants will be randomized between pacing distally in the coronary sinus and right atrial appendage. Randomization is stratified for all participating centers. Conventional dual-chamber pacemakers with advanced home monitoring functionality will be implanted. The ventricular lead will be implanted in the right ventricular apex. The first three months of the 36-month follow-up period are considered as run-in time. During the pre-randomization visit and follow-up, an interview, electrocardiogram and pacemaker assessment will be performed, prescribed antiarrhythmic medication will be reviewed and patients will be asked to complete an SF-36 questionnaire. An echocardiographic examination will be conducted in the pre-randomization phase and at the end of each follow-up year. Home monitoring will be used to send daily reports in case of atrial fibrillation episodes.

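### Randomisation is stratified by centre, but the tests named for AF recurrence cannot take centre into account, which gives up a modest amount of power if centres differ

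*Protocol article*

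**What the plan says.** Allocation: the Randomization section of the protocol article says "Randomization is stratified for all participating medical centers", and the Methods/Design paragraph of the abstract agrees: "Randomization is stratified for all participating centers". The article gives no number of centres, block scheme or allocation ratio.

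Analysis, all from the Statistical analysis section:

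- Yes/no recurrence: "Therefore the Fisher’s exact test will be used for this categorical data to assess the difference in AF recurrence".
- Count and duration: "Continuous data regarding duration and total number of AF recurrences will be analyzed by the" Student's t-test.
- Time to event: "Kaplan-Meier curves will be constructed to compare event-free survival between both groups". No test or model accompanies the curves.
- Secondary outcomes: "Secondary outcomes will be analyzed by a multivariate analysis". Its covariates are not given.
- Significance level: a P "value of 0.05 is considered to be statistically significant".

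The article never says that centre enters a primary comparison.

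**The concern.** Stratified allocation pays off when the analysis uses the strata. If the arms are balanced inside each centre, differences between centres cancel out of the treatment contrast. A test without centre still counts those differences as noise. Its standard error is then larger than the real uncertainty, its p-values run high, and some of the efficiency bought by stratifying is not collected.

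Centre differences are plausible in both arms. Each local team has three months of run-in to settle the drug regimen and device settings (Run-in time), and AF detection depends on sensing and programming (Limitations). The article does not quantify any of this.

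What is at stake is efficiency in the main comparison of the two pacing sites. Validity is not threatened.

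**Working it through.** **Plan's own figure.** The Sample size section gives 300 patients for power 0.8. This cannot be reproduced, because no effect size, event rate or standard deviation is stated. Assuming 150 per arm and two-sided 0.05, 80% power corresponds to a standardised difference of 0.3235, or for proportions to about 50% v 34%. These back-solved values are used below.

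**Assumptions, none given in the article.** Allocation is exactly balanced within centre, the total outcome SD is 1, and centre accounts for a share ICC of the variance.

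**Formulas for the t-test.**

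- Reported SE = sqrt(2/150) = 0.1155. True SE = 0.1155 × sqrt(1-ICC). The ratio is 1/sqrt(1-ICC).
- True size = 2 × [1 - Phi(1.96/sqrt(1-ICC))].
- The effect divided by the reported SE is 0.3235/0.1155 = 2.80. Power without centre = Phi((2.80 - 1.96)/sqrt(1-ICC)). Power with centre = Phi(2.80/sqrt(1-ICC) - 1.96).

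| ICC | SE ratio | True size | Power, t-test | Power, with centre | Gap (points) |
|---|---|---|---|---|---|
| 0 | 1.000 | 0.050 | 80.0% | 80.0% | 0 |
| 0.01 | 1.005 | 0.049 | 80.1% | 80.4% | 0.3 |
| 0.05 | 1.026 | 0.044 | 80.6% | 82.0% | 1.4 |
| 0.10 | 1.054 | 0.039 | 81.3% | 84.0% | 2.7 |
| 0.20 | 1.118 | 0.028 | 82.7% | 88.0% | 5.3 |

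**Simulation with balance within centre** (10 centres of 30 assumed, 20,000 runs). At ICC 0.05, 0.10 and 0.20 the t-test's size was 0.046, 0.041 and 0.032, and the power gaps were 1.4, 2.4 and 5.1 points. At ICC 0 both analyses had 79.6% power.

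**Simulation with simple randomisation inside each centre.** The t-test's size stayed between 0.049 and 0.052 at every ICC. Power without v with centre was 79.7% v 78.4% at ICC 0, 79.8% v 80.5% at 0.05, 80.3% v 82.9% at 0.10 and 80.4% v 86.6% at 0.20. The SE is then not overstated. Adjustment gains power from an ICC of about 0.05, and with no centre effect it costs a little.

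**Yes/no outcome** (50% v 34%, balance within centre, 8,000 runs). The uncorrected chi-square test is included to separate the effect of centre from Fisher's own conservatism.

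| ICC (approx.) | Power, Fisher | Power, chi-square | Power, Cochran-Mantel-Haenszel |
|---|---|---|---|
| 0 | 78.1% | 81.7% | 81.5% |
| 0.04 | 78.3% | 81.8% | 82.1% |
| 0.08 | 78.8% | 81.9% | 83.2% |
| 0.15 | 79.5% | 82.8% | 85.7% |

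Fisher trails Cochran-Mantel-Haenszel by about 3.4 points with no centre effect at all. The part due to centre, chi-square against Cochran-Mantel-Haenszel, is about 0.3, 1.3 and 2.9 points at ICC 0.04, 0.08 and 0.15.

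**The case against.** **The article is a summary, and the full protocol or SAP may bring centre in.** Which stratification factors enter a model is often settled there. But the article does not leave the method open. It names two tests that have no place for centre, so a later document could add centre only by departing from them. This objection softens the point without removing it.

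**Overstated standard errors are not established.** This stands. The word stratified does not by itself mean blocked, and the simple-randomisation results show size near 5% without enforced balance. The overstated SE is therefore conditional, and so is any claim that intervals are too wide. For Fisher's test the effect is on the p-value.

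**The centre effect is unknown.** This also stands. The loss is nil at ICC 0 and 0.3 points at 0.01. A reader might take the choice of coronary sinus lead by local availability (Implantation) as proof that centres differ. That choice exists only in the coronary sinus arm, so it suggests a treatment effect that varies by centre. It is not a difference shared by both arms, and adjusting for centre would not remove it.

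**A reader might infer that the trial is underpowered.** If 80% were the power of a centre-adjusted test, the unadjusted test would have Phi(2.80 - 1.96/sqrt(1-ICC)), which is 78.5% at ICC 0.05 and 76.9% at 0.10. The Sample size section does not say that centre was in the calculation. If the 300 was set for an unadjusted test, the t-test keeps 80.6% and 81.3%. The documents do not support a fall below 0.8.

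**Fisher's conservatism is a separate matter.** It comes from the discreteness of the test and should not be counted as a cost of ignoring centre.

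**Conclusion.** The point holds as a modest efficiency loss. The mismatch between allocation and analysis is in the text. Its size is not, because it rests on an assumed ICC, on balance within centre for the overstated SE, and on 150 per arm with two-sided 0.05. For ICC 0.01 to 0.10 the t-test gives up about 0.3 to 2.7 power points against a centre-adjusted analysis, and nothing at ICC 0. The centre-related loss for the yes/no outcome is similar.

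The error is in the conservative direction. A reader might infer inflated false positives or a biased comparison, but the calculations show size at or below about 5%. The change is worth making because it costs almost nothing, not because the result would otherwise be unsound.

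**What to change.** In the Statistical analysis section, state that the primary between-arm comparisons take account of centre:

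- yes/no recurrence: Cochran-Mantel-Haenszel test stratified by centre, in place of Fisher's exact test;
- number and duration of recurrences: a linear (or count) model with centre, in place of the t-test;
- event-free survival: a centre-stratified log-rank test alongside the Kaplan-Meier curves.

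State in advance how small centres are handled, either pooled by a written rule or fitted as a random effect. This matters most if allocation is not blocked, since fitting every centre then cost about 1.3 points in the simulation with no centre effect (79.7% v 78.4%, before rounding). It would help to state in the Randomization section whether blocks are used. Centre adjustment alone does not require replacing the primary methods more widely.

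The cost is analysis wording only. The trial website already gives each centre its own part (Dedicated website), so centre is on record, and no patients or data are added. Enrolment had not begun when the article was written (Trial status), so the change could precede any outcome data.

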### Study groups

The study consists of two study arms; an atrial lead will be positioned in RAA position (group I) or in the dCS (group 2). Crossover will not be feasible due to the design of the study. All participants in both groups will have a ventricular lead implanted in the right ventricular apex (RVA). A conventional dual chamber with HM functionalities will be implanted in all patients.

